## Aims of the Study

The primary objective of Projecte Moviment is to examine the effect of CCT, AE, or COMB on cognitive outcomes in healthy physically inactive older adults. The primary hypotheses sustaining this goal are:

1.Computerized cognitive training – 5 times per week for 3 months – will improve general cognitive function as well as trained cognitive functions (executive function, processing speed and memory) measured by composite scores using a battery of validated neuropsychological tests at 3 months compared to a control group.2.Aerobic exercise – 5 times per week for 3 months – will improve executive function, attention-processing speed and memory measured by composite scores using a battery of validated neuropsychological tests at 3 months compared to a control group.3.Combined training – 5 times per week for 3 months – will show greater improvements in general cognitive function, executive function, attention-processing speed and memory measured by composite scores using a battery of validated neuropsychological tests at 3 months compared to a control group.

The secondary objectives of Projecte Moviment are: (a) to determine the effects of these interventions on psychological status and subjective performance on daily activities, CRF, brain structure and function and physiological molecular correlates; (b) to identify genetic, demographic, physiological and brain variables that might predict the effect of the intervention; (c) to identify the association between cognitive effects and other psychological, physiological correlates. Specific hypotheses for each objective will be specified in each article when reporting results. General secondary hypotheses include:

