## Methods

### Study Oversight and Schedule

Projecte Moviment is a multi-center, single-blind randomized controlled trial that started November 2015 with the aim of recruiting 140 participants distributed in four parallel groups (one control group, *n* = 20; three intervention groups, *n* = 40 each). All participants give their written informed consent and are assessed at baseline and 3 months later, immediately after the intervention (Figure 1). This study is led by the Faculty of Psychology of the University of Barcelona in collaboration with Institut Universitari d’Investigació en Atenció Primària Jordi Gol, Hospital Germans Trias i Pujol and Institute Guttmann; it was approved by the responsible ethics committees following the Declaration of Helsinki.

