### Analyses

#### Power Analysis

The sample size was determined considering previous studies (Erickson et al., 2011) and the effect size and the standard error of cardiovascular interventions on all cognitive tasks reported in a previous meta-analytic study (Colcombe and Kramer, 2003). We also considered the following assumptions: bilateral contrasts and an effect size of 0.4 using the Tukey–Kramer multiple comparison test at 0.05 significance level with a common standard deviation within a group of 0.3. In order to have at least 80% statistical power to answer the 3 primary aims of the project, we need 18 subjects in the control group and 36 for CCT, AE, and COMB groups, respectively. Assuming 10% of lost to follow up (Rahe et al., 2015), we need a total sample size of 139 subjects (control group *n* = 19, intervention groups *n* = 40). Sample power has been computed using PASS 14 Power Analysis and Sample Size Software.

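### The three primary hypotheses are all against control, but the only multiplicity method named, Tukey–Kramer, protects six pairs; Dunnett's test would match the hypotheses and recover power at no cost in participants

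*Protocol article*

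**What the plan says.** The Aims of the Study section of the Protocol article lists three primary hypotheses, for CCT, AE and COMB. Each is worded as an improvement "measured by composite scores using a battery of validated neuropsychological tests at 3 months compared to a control group". The expectation of larger gains with COMB is also set against control, not against a single intervention. Contrasts between active conditions appear only among the general secondary hypotheses (numbers 2 and 4).

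The Power Analysis section assumes "bilateral contrasts and an effect size of 0.4 using the Tukey–Kramer multiple comparison test at 0.05 significance level". For the spread of the outcome it takes a "common standard deviation within a group of 0.3", and the goal it sets is "at least 80% statistical power to answer the 3 primary aims of the project". Its result is that "we need 18 subjects in the control group and 36 for CCT, AE, and COMB groups, respectively". The recruitment target in Study Oversight and Schedule is "one control group, *n* = 20; three intervention groups, *n* = 40 each".

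The Statistical Analyses section sets a two-sided 0.05 threshold and says that multiple comparisons will be corrected for, without naming a method. Tukey–Kramer appears only in the sizing.

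**The concern.** A multiplicity method should cover the comparisons that carry the primary claims. Four arms form six pairs. Tukey–Kramer controls the family-wise error over all six, so the three control contrasts pay, through a higher critical value, for three between-intervention pairs on which no primary hypothesis depends. Dunnett's test gives the same 5% family-wise protection for exactly the three contrasts stated.

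A second feature works in the same direction. The control arm enters every primary contrast, yet it is half the size of each other arm, and the article gives no reason. At stake is the precision of the primary comparisons at a fixed total.

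**Working it through.** **Inputs.** From Power Analysis: evaluable arms 18/36/36/36 (total 126, so 126 − 4 = 122 degrees of freedom), two-sided 0.05, effect size 0.4, SD 0.3. From Study Oversight and Schedule: recruited arms 20/40/40/40. From Aims of the Study: three contrasts, each against control.

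**Critical values.**
- Tukey–Kramer: the studentised range quantile for 4 groups and 122 df, divided by √2, is 2.605.
- Dunnett at 18/36/36/36, by simulation: about 2.33 (runs gave 2.334 to 2.339).

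**Standard error of a control contrast, in SD units.** √(1/18 + 1/36) = √0.0833 = 0.2887. For a true difference of d SDs the noncentrality is d/0.2887, and power follows from the noncentral t with the critical value above.

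**Reproducing the plan's 18/36.** The article does not say what kind of effect size 0.4 is, so several readings were tried under Tukey–Kramer.
- Raw difference 0.4 over SD 0.3 (1.33 SD): power at 18/36 is 97.7% per contrast and about 95% for all three. For 80%, 11 controls (per contrast) or 13 (all three) would be enough, so this reading does not give 18.
- Cohen's f = 0.4 with equal intervention means: the control share is 18/126 = 1/7, so the difference is 0.4 × 0.3/√((1/7)(6/7)) = 0.343, or 1.14 SD. Power for all three contrasts jointly is 79.1% with 17 controls and 82.4% with 18. This gives 18/36 exactly, but the pattern of means is an assumption.
- Difference of 1.0 SD (assumed), per contrast: 77.5% with 17 controls and 80.3% with 18. This also gives 18.
- Standardised difference of 0.4: 11.6% at 18/36.

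**Tukey–Kramer against Dunnett, same arms, power per control contrast.**

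| Reading of the effect | Difference | Tukey–Kramer | Dunnett |
|---|---|---|---|
| 0.4 raw over SD 0.3 | 1.33 SD | 97.7% | 98.8% |
| Cohen's f = 0.4, equal intervention means | 1.14 SD | 91.0% | 94.6% |
| Assumed 1.0 SD | 1.0 SD | 80.3% | 87% |
| 0.4 as a standardised difference | 0.4 SD | 11.6% | 17.5% |

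On the Cohen's f reading, joint power for all three contrasts goes from 82.3% to 88.9%. The difference detectable with 80% power per contrast falls from 0.997 SD to 0.918 SD.

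**Allocation.** The variance factor of a control contrast at the recruited sizes is 1/20 + 1/40 = 0.0750. With equal arms of the same total of 140 it is 2/35 = 0.0571. The ratio is 0.0750/0.0571 = 1.31, so the planned variance is about 31% larger. Between two interventions the factors are 2/40 = 0.050 and 2/35 = 0.057, so equal arms would cost precision there.

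**The case against.** **Is the trial underpowered because of this?** A reader might infer so, especially after trying a smaller effect: at 0.8 SD, power is 57% with Tukey–Kramer and 67% with Dunnett. But 0.8 SD appears nowhere in the article. At 1.0 SD, at f = 0.4 and on the raw 0.4/0.3 reading, the plan meets its 80% target with Tukey–Kramer. Power falls short only for differences below about 1.0 SD. That turns on the undefined effect size, which is a separate matter from the choice of test.

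**Is the loss certain in the analysis?** No. Tukey–Kramer is tied only to the sample size, and the analysis section leaves the method open. If the analysis uses Dunnett, sizing on Tukey–Kramer was merely conservative. Carrying the sizing method forward is the likelier course, but the text does not say so.

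**Is all-pairs protection justified?** Partly. The condition-by-time step in Statistical Analyses is described as serving to compare interventions, and secondary hypotheses 2 and 4 contrast active conditions. That supports Tukey–Kramer for secondary comparisons. It does not bring those pairs into the primary family.

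**Should the control arm be enlarged now?** The imbalance may tempt a reader to say so, but the documents do not support it. Larger intervention arms serve the stated aims on predictors and correlates of response. The secondary analyses use a per-protocol sample with at least 80% adherence, and the Discussion expects that adherence may be low. If half of the intervention participants adhered (an assumption), the control-contrast factor would be 1/20 + 1/20 = 0.100 at 20/40 and 1/35 + 1/17.5 = 0.086 with equal arms, a gain of only 14%. The factor between interventions would worsen from 0.100 to 0.114. Replacing the stratified list during a trial that began in November 2015 would also confound arm with period.

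**Conclusion.** The point holds as an efficiency loss. The named multiplicity method does not match the three primary hypotheses, and it raises their critical value from about 2.33 to 2.605. The cost in power per contrast is about 1 point on the raw 0.4/0.3 reading, about 4 points at f = 0.4 (about 7 for all three jointly), about 7 points at 1.0 SD and about 6 points at 0.4 SD. The f reading assumes equal intervention means, and the 1.0 SD and 0.4 SD differences are assumed effects. All figures assume 126 evaluable participants and a common SD. The loss is certain for the sizing; it reaches the results only if Tukey–Kramer is also used in the analysis. Separately, the 1:2 control allocation raises the variance of each primary contrast by about 31% compared with equal arms of the same total. That is a limitation to state, not a reason to reallocate.

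**What to change.** In Power Analysis and Statistical Analyses, name Dunnett's many-to-one test against control for primary hypotheses 1 to 3, applied within each cognitive outcome at a two-sided family-wise level of 0.05. Label between-intervention comparisons secondary, and keep Tukey–Kramer for those if wanted. Dunnett deals with the number of arms only; any correction across cognitive outcomes is a separate matter.

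The cost is wording. It needs no further participants, and it should be settled before results by arm are seen. The one downside is that between-intervention comparisons then fall outside the primary family, where no primary hypothesis places them anyway. Add a sentence to the limitations that the smaller control arm widens the confidence interval of every primary contrast, and leave the allocation unchanged.

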#### Statistical Analyses

Addressing the primary objective, statistical procedures will be performed with IBM SPSS Statistics 24 and R Environment. The distribution of raw scores will be examined in order to assess data quality (i.e., outliers, skewness) and we will obtain sample *z*-scores for all cognitive tests. Five primary domains will be calculated by adding *z*-scores – executive function, memory, language, attention-speed, and visuospatial function – which will be split into nine secondary domains in order to assess specific changes within each domain – inhibition, fluency, working memory, verbal memory, visual memory, language, attention, speed and visuospatial function (see Table 3). Domains will be based on the literature (Strauss and Spreen, 1998; Lezak et al., 2012) given the fact that a principle component analysis would not be appropriate for our sample size.

In order to test our primary hypotheses, we will conduct an intention-to-treat (ITT) analysis considering data from all randomized participants, including those that complete and drop-out, in order to prevent attrition bias. An adequate method of imputation will be applied and informed. Parametric or non-parametric tests will be chosen regarding the fitting of data to statistical requirements of the tests and we will follow a coherent pipeline to explore variance: (a) comparison of baseline values between groups to identify potential variables to adjust further analyses; (b) comparison of variables at different time-points for each group to identify the independent effect of each condition; (c) identification of significant cross-time correlations in order to determine whether it is necessary to control for baseline measures; (d) interaction between conditions and time-points to compare interventions. Sex, age, and years of education will be considered covariates beforehand and a two-tailed *p*-value < 0.05 will be set as the significant threshold and the corresponding correction for multiple comparisons will be applied. In a second phase, we will define a per-protocol (PP) sample including only subjects that finished the intervention with at least 80% adherence and we will reproduce the same pipeline. In case of high disparity between ITT and PP results, we will analyze potential variables related to that discrepancy.

We will analyze our secondary hypotheses following the same pipeline in the per-protocol sample to guarantee that we will be studying the effects of the intervention on the previously described outcomes. We will examine potential mediator effects through relationships between primary and secondary outcomes accounting for the intervention condition using adequate correlational methods and linear mixed models. Structural neuroimaging data will be first processed studying whole brain, hippocampus and frontal lobe volumes and white matter microstructure. In a second phase, connectivity and white matter lesions will be analyzed. Data will be published in several papers where detailed procedures and software packages will be described.

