### Randomization

Participants are randomly assigned to the groups stratified by sex, age, and education. The allocation sequence consists of a random list of these variables all combined and was generated by a statistician. The intervention staff is responsible for the allocation and informs participants at the first intervention visit. Assessors are blinded to the sequence and the group assignment of the participants. Blinding will only be broken for medical reasons.

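### The test and the baseline adjustment are both chosen from trial data, although the covariates are fixed, so composites could be analysed with different adjustment and effect measures

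*Protocol article*

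**What the plan says.** The Statistical Analyses section of the protocol article sets out the primary intention-to-treat analysis in one paragraph. On the choice of test it says: "Parametric or non-parametric tests will be chosen regarding the fitting of data to statistical requirements of the tests". Step (c) of the pipeline then looks for significant correlations between time points "in order to determine whether it is necessary to control for baseline measures". Step (d) compares the interventions through the interaction of condition and time.

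The same paragraph also states: "Sex, age, and years of education will be considered covariates beforehand". These are the stratification factors in the Randomization section: "Participants are randomly assigned to the groups stratified by sex, age, and education".

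No non-parametric test is named. There are two time points, baseline and 3 months. The primary outcomes are five domain composites and a global score (Primary Outcomes; Table 3), with nine secondary domains beneath them.

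**The concern.** The paragraph makes two choices depend on the trial data (which family of test, and whether to adjust for baseline) and fixes a third thing, the covariates. They do not fit together. The usual rank tests (Mann–Whitney, Kruskal–Wallis, Wilcoxon, Friedman) have no place for sex, age or education. If the fit check sends memory to a rank test and executive function to a linear model, one result is adjusted for the stratification factors and the other is not. One is a mean difference and the other a shift in ranks. A reader could not set the domain results side by side.

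Step (c) leaves the baseline score, usually the strongest predictor of the 3-month score, to a significance check. In a randomised comparison with about 18 evaluable controls serving all three contrasts, that precision should be secured in advance.

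This is more than a detail left to an analysis plan. The article states the data-driven rule, and a later plan that fixed one model would depart from it.

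**Working it through.** **1. The plan's own figure.** Inputs from the Power Analysis section: 18 controls and 36 per intervention arm; "bilateral contrasts and an effect size of 0.4"; an SD of 0.3 in every group; Tukey–Kramer comparisons at the 0.05 level; and a target of "at least 80% statistical power to answer the 3 primary aims of the project". Read 0.4 as Cohen's f:
- SD of the means = 0.4 × 0.3 = 0.12.
- Control share = 18/126 = 1/7.
- Difference from control = 0.12/√(1/7 × 6/7) = 0.12/0.350 = 0.343, which is 0.343/0.3 = 1.14 SD.
- Simulated Tukey–Kramer power for all three control contrasts together is 0.824 at 18/36 and 0.790 at 17/34, so 18/36 is reproduced.
- Total: 126 × 1.1 = 138.6, rounded up to the stated 139.

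Read as a raw difference, 0.4/0.3 = 1.33 SD, and the same power is 0.948.

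**2. What each route can carry with two time points.**

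| Method | Sex, age, education | Baseline score | Condition by time |
|---|---|---|---|
| Linear model or mixed model | yes | yes | yes |
| Rank test on 3-month scores | no | no | no |
| Rank test on change scores | no | yes | yes |
| Rank ANCOVA | yes | yes | yes, as an adjusted arm comparison |

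Only the covariates are lost on both common rank routes.

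**3. What guaranteed baseline adjustment is worth.** Assumed, not in the documents: a 0.6 SD effect, baseline-to-3-month correlation ρ of 0.5 or 0.7, normal data, unadjusted two-sided 0.05. Other covariates are left out of both methods. The non-centrality is 0.6/(s × √(1/18 + 1/36)) = 0.6/(0.2887 × s), where s is the residual SD in units of the 3-month SD.

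| ρ | Method | Residual variance | Non-centrality | Power (non-central t) |
|---|---|---|---|---|
| 0.5 | Change score | 2(1 − 0.5) = 1.00 | 2.08 | 53% |
| 0.5 | ANCOVA | 1 − 0.25 = 0.75 | 2.40 | 65% |
| 0.7 | Change score | 2(1 − 0.7) = 0.60 | 2.68 | 75% |
| 0.7 | ANCOVA | 1 − 0.49 = 0.51 | 2.91 | 81% |

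A simulation under the same assumptions gave 65% and 81% for ANCOVA and 55% and 76% for the change-score test. The gain is therefore about 10 to 12 points at 0.5 and 5 to 6 at 0.7.

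**4. What the rank routes do to power.** Simulated, 18 against 36, 0.6 SD, covariates assumed to explain 20% of variance, ρ = 0.5 / 0.7 / 0.8:

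| Method | Normal data | Skewed (lognormal-type) data |
|---|---|---|
| ANCOVA | 64 / 80 / 92% | 69 / 79 / 88% |
| Rank test, 3-month score | 50 / 50 / 52% | 75 / 75 / 75% |
| Rank test, change | 48 / 72 / 89% | 67 / 85 / 95% |
| Rank ANCOVA | 61 / 76 / 88% | 86 / 92 / 97% |

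Applying the switch as a rule (Shapiro–Wilk, ρ = 0.7, ANCOVA or a rank test on 3-month scores) moved power from 80% to 77% with normal data and from 78% to 75% with skewed data. Type I error was 5.3% and 5.2%. A further run at ρ of 0.5 and 0.7 found a loss of about 1 point with normal data and a gain of 7 to 18 points with strong skew.

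**5. When step (c) would withhold adjustment.** The smallest significant correlation is t/√(t² + n − 2). Pooled, n = 126: 1.979/√(3.917 + 124) = 0.175. In the control arm alone, n = 18: 2.120/√(4.494 + 16) = 0.468. The article does not say which applies.

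**The case against.** Several stronger readings are tempting, and the checks do not support them.

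- *Rank tests lose baseline and the interaction.* Not necessarily. With two time points, a rank test on change scores uses the baseline and tests condition by time. Both are lost only if 3-month scores alone are ranked, and the article does not say that.
- *Power falls.* Not in general. The large losses come from normal data, which the rule would mostly leave with the linear model. With skewed data the rank route is sometimes better and sometimes worse.
- *Error control is weakened.* The simulated switch kept type I error near 0.05. The effect of step (c) on type I error was not tested.
- *The adjusted analysis cannot be run on ranks.* Rank ANCOVA would keep both covariates and baseline, and the text does not exclude it. An analysis plan might name it.

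Two further points limit the size. At the planning effect of 1.14 SD, even ρ = 0.5 gives 1.143/0.2887 = 3.96 and about 97% power for the change-score test, against over 99% for ANCOVA. And if step (c) is applied to the pooled sample, correlations of 0.5 to 0.7 lie far above 0.175, so adjustment would nearly always follow. Applied in the control arm, a true correlation of 0.5 lies just above the 0.468 threshold, and the check could readily fail.

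What stands is the stated rule itself: covariates fixed in advance, a test family that may be unable to carry them, and baseline adjustment that is conditional.

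**Conclusion.** The concern holds as a matter of pre-specification and precision. As written, the primary composites could be reported with different adjustment and different effect measures, and baseline adjustment is not guaranteed. Where adjustment is omitted, the cost with normal data is about 5 to 12 percentage points of power relative to ANCOVA. That figure rests on an assumed 0.6 SD effect and a correlation of 0.5 to 0.7, neither of which the article gives. It is negligible at the effect that reproduces the stated sample size. No general loss of power from rank tests, and no inflation of type I error, has been shown.

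**What to change.** Replace the test-choice sentence and step (c) with one primary model for every composite: 3-month score on arm, baseline score, sex, age and education, or the equivalent mixed model. State in advance what happens if residuals are non-normal: a named transformation, or heteroscedasticity-robust or bootstrap confidence intervals. Keep a covariate-adjusted rank analysis, such as rank ANCOVA, as a sensitivity analysis for all composites.

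The change is to wording; the data and the software (SPSS and R) stay the same. Baseline adjustment uses one degree of freedom. The one real downside is that under marked skew the linear model can have less power than a rank method: 79% against 92% for rank ANCOVA in the skewed simulation at a correlation of 0.7. A transformation may recover some of this; bootstrap intervals alone would not.

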## Discussion

Healthy aging is a current social challenge. Lifestyle behaviors such as cognitive training and exercise have a positive impact on health, brain and cognition with the possibility of greater benefits when they are combined. Despite this evidence, there are still many questions remaining unanswered. Questions about the type of activity, length, frequency, duration, and intensity required to observe a cognitive effect, the potential individual predictors of response to the intervention, the relationship between physiological molecular correlates, and structural and functional brain changes and cognitive and psychological benefits remain unclear. Projecte Moviment is a multi-domain intervention trial based on prior evidence that aims to understand the effects of CCT, AE, and COMB on cognitive and psychological outcomes compared to a passive control group and determine related biological correlates as well as significant predictors of their effect. We aim to describe what type of change these specific interventions may produce on biological, cognitive and psychological outcomes at 3 months. These results may support the literature that is currently examining the timeline of the effects of these interventions (Stimpson et al., 2018; Cabral et al., 2019) on cognition and trying to identify potential related modifiers (Barha et al., 2017; Northey et al., 2017). We expect to find changes in physiological molecular correlates as well as structural and functional brain outcomes within each intervention group and determine how they differ across groups. Those changes may be related to potential cognitive and psychological improvements depending on adherence, characteristics of the intervention and other individual variables.

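### Step (b) of the analysis pipeline treats within-arm pre-post change as the effect of a condition; it should be descriptive only, with effect claims resting on the condition-by-time contrast in step (d)

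*Protocol article*

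**What the plan says.** The Protocol article, Statistical Analyses, introduces the pipeline with this purpose: "In order to test our primary hypotheses, we will conduct an intention-to-treat (ITT) analysis considering data from all randomized participants". Two of its four steps matter here:

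- Step (b): "comparison of variables at different time-points for each group to identify the independent effect of each condition".
- Step (d): "interaction between conditions and time-points to compare interventions".

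The same section repeats the pipeline in the per-protocol sample, and the text that follows applies it to the secondary hypotheses.

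Under Aims of the Study, each primary hypothesis concerns cognition "measured by composite scores using a battery of validated neuropsychological tests at 3 months compared to a control group". The control arm is a waiting list (Control Group). The neuropsychological battery is given at baseline and again after the intervention, apart from the vocabulary subtest (Assessments, Table 2 and its first footnote).

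Study Oversight and Schedule describes the trial "with the aim of recruiting 140 participants distributed in four parallel groups", with 20 in control and 40 in each intervention arm. Power Analysis gives 18 and 36 evaluable. It bases them on a between-group procedure, "using the Tukey–Kramer multiple comparison test at 0.05 significance level".

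**The concern.** Step (b) gives a causal meaning to a comparison with no control in it. People tested twice on the same battery may score differently the second time whether or not they were treated. Time trend and regression to the mean also enter the change. The waiting-list arm is there to remove these components, and step (b) does not use it.

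The wording also divides the work badly. It gives the identification of effects to the within-arm tests and leaves the interaction the task of comparing interventions. An analyst following the text could report that a condition had an effect because its own pre-post test was significant.

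Unequal allocation adds to this. If all arms gain equally, a larger arm reaches significance more often than a smaller one. A set of within-arm p-values can then look like intervention benefit when nothing differs between arms.

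**Working it through.** **Planned arm sizes.** The evaluable sizes of 18 and 36 can be reproduced. Power Analysis states "bilateral contrasts and an effect size of 0.4", an SD of 0.3, Tukey–Kramer at 0.05 and at least 80% power. Reading 0.4 as an allocation-weighted ANOVA effect size with 1:2:2:2 allocation, the control-versus-intervention difference is 0.4 × 0.3 / √((1/7)(6/7)) = 0.343. Simulated power for all three contrasts with control is then 79.1% at 17/34 and 82.4% at 18/36, so 18/36 is the smallest size that meets 80%. With 10% loss, 18/0.9 = 20 and 36/0.9 = 40, total 140. (Power Analysis prints 19 and 139; the difference does not matter here.) These sizes belong to between-group contrasts, not to within-arm tests.

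**Assumptions for the check.** The article gives no retest gain, so a range is used. Every arm has the same mean gain g, in units of the SD of change, and there is no treatment effect. Arms are independent, tests are two-sided at 0.05, and z-scores share a common baseline reference.

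**Formulas.**

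- Chance of a significant paired t-test in an arm of size n: p(n) = 1 − F(c; n−1, g√n) + F(−c; n−1, g√n), where F is the noncentral t distribution function and c the two-sided critical value on n−1 degrees of freedom.
- Chance that at least one of three intervention arms is significant and control is not: (1 − p_C) × [1 − (1 − p_I)³].

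**Example, g = 0.3.** The noncentrality is 0.3 × √18 = 1.27 in control and 0.3 × √36 = 1.80 in an intervention arm, giving p_C = 0.225 and p_I = 0.417. Then (1 − 0.225) × [1 − 0.583³] = 0.775 × 0.802 = 0.62. With control also at 36, it is 0.583 × 0.802 = 0.47.

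| Common gain (SD of change) | Control, n=18 | Intervention arm, n=36 | At least one intervention arm significant, control not | Same, control n=36 |
|---|---|---|---|---|
| 0 | 5.0% | 5.0% | 13.5% | 13.5% |
| 0.2 | 12.6% | 21.5% | 45.1% | 40.5% |
| 0.3 | 22.5% | 41.7% | 62.2% | 46.7% |
| 0.4 | 36.0% | 64.6% | 61.1% | 33.9% |
| 0.5 | 51.6% | 83.1% | 48.1% | 16.9% |
| 0.8 | 89.2% | 99.7% | 10.8% | 0.3% |
| 1.0 | 97.9% | 100.0% | 2.1% | 0.0% |

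**Direction.** For one intervention arm against control at g = 0.3, the arm is significant and control is not in 32.3% of trials; the reverse occurs in 13.1%. With equal arm sizes the two would be equally likely.

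**Multiplicity.** The plan promises a correction without naming it in this article. At an assumed 0.0125 (Bonferroni over four arms), within-arm significance is 9.1% v 21.9% at g = 0.3 and 28.5% v 64.4% at g = 0.5. The tilt remains.

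**Between-group test.** Under the same equal gains (0, 0.3 and 0.5), simulated type I error is 4.9% to 5.0% for one intervention arm against control and 4.9% to 5.2% for the four-group condition-by-time test. Step (d) is not affected.

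**The case against.** The strongest reply is that the valid analysis is already planned. Step (d) is a condition-by-time test, the hypotheses are stated against control, and the sample size rests on between-group comparisons. Step (b) covers every condition, the waiting list included, and may only mean looking at each arm separately before comparing them. This stands as far as the primary conclusion goes: it need not depend on (b). It does not rescue the purpose clause, which still says that a within-arm test identifies a condition's effect.

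A reader might infer more than the article supports, in three ways:

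- **That the plan would credit the interventions whenever all arms improve equally.** No section says that an effect is claimed when an intervention arm is significant and control is not. That rule is an inference; the wording permits it but does not prescribe it.
- **That the 62% is built in by the half-size control arm.** An equal-size control would still give 47% at the same gain, mainly because three arms have three chances. The gain is also assumed, and 62% is near the peak of a curve running from 13.5% at zero gain to 2% at 1.0.
- **That other sections rely on within-group change alone.** The Discussion says "We expect to find changes in physiological molecular correlates as well as structural and functional brain outcomes within each intervention group", but the sentence goes on to differences across groups. Blood-Sample Data selects biomarkers for ELISA on differences both within and between groups, and this is an assay screen, not an efficacy claim.

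The z-score scaling is a further limit. If scores were standardised separately at each visit, a common gain would drop out. Each arm's change would then be relative to the pooled sample, which is still not that condition's own effect.

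**Conclusion.** The point holds as a correction to the meaning given to step (b). Within-arm pre-post tests cannot identify the effect of a condition in this design, and they do not address the stated hypotheses. The planned test in (d) is sound and keeps its error rate.

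How misleading (b) could be depends on a retest gain that the article does not give. With no common gain there is no tilt between arms. At gains of 0.2 to 0.5 SD of change, an intervention arm is about 1.6 to 1.9 times as likely as control to show a significant change. At 0.8 nearly every arm does. The smaller control arm explains little of the discordant pattern at a gain of 0.2 (45% v 41% with an equal-size control) and most of it at 0.5 (48% v 17%). These figures rest on independent arms, 18 and 36 evaluable, two-sided 0.05 and a common baseline reference for the z-scores.

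**What to change.** In Statistical Analyses:

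1. Reword step (b) as a description of change within each arm, reported as mean change with 95% confidence interval.
2. Delete the purpose clause that presents this as a condition's effect.
3. State that all effect claims, including those in the per-protocol sample and for the secondary hypotheses, rest on the intervention-versus-control contrast of change in step (d).

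In Blood-Sample Data, at most add that within-group change alone does not count as an intervention effect.

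The cost is a few sentences. No data collection, sample size or planned between-group test changes.
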